**3.5.4 Nausea**

Routine premedication for nausea is not necessary, but symptomatic patients should be treated with standard antinausea/antiemetic therapy as necessary.

If the patient vomits after taking the tablets, the dose is replaced only if the tablets can actually be seen and counted.

**3.6 Dosing delays/dose modifications**

Starting dose and dose modifications for unacceptable toxicity are listed in Table 6. For toxicity that is thought to be related to lapatinib, the daily dose of lapatinib will be decreased according to the schedule displayed in the Table 7.

Dose adjustments are to be made according to the greatest degree of toxicity. Toxicities will be graded using NCI Common Terminology Criteria for Adverse Events (CTCAE) version 3.0.

The most common toxic effects of lapatinib are:

**Metabolism and nutrition disorders:**

Anorexia

**Cardiac disorders:**

Decreased ejection fraction

**Gastrointestinal Disorders:**

Diarrhea which may lead to dehydration; nausea, and vomiting.

**Skin and subcutaneous tissue disorders:**

Rash (including dermatitis acneiform)

**General disorders and administration site conditions:**

Fatigue

**3.6.1 Dose Delays and Dose Reductions**

Treatment may be delayed, up to 2 weeks, to allow for resolution of toxicity except in the event of NCI CTCAE Grade 3 or 4 left ventricular cardiac dysfunction or NCI CTCAE Grade 3 or 4 interstitial pneumonitis. The Investigator must consult the GSK Medical Monitor prior to continuing therapy for any subject requiring a delay of more than 2 weeks for unresolved toxicity, but in general, such subjects should be withdrawn from the study. If treatment is delayed for reasons other than toxicity (i.e., unplanned travel or vacation, or lack of transportation to the site) and the subject has insufficient investigational product available, the subject should resume the usual dosing schedule once drug supply has been made available. However, if the subject has been off therapy for more than 2 weeks, the Investigator must consult the GSK Medical Monitor prior to continuing therapy.

Dose reduction for drug-related toxicity is permitted; however the GSK Medical Monitor must be consulted prior to implementing any change in dosing. Only one dose reduction is permitted per subject and subjects should not be rechallenged to a higher dose level. If a NCI CTCAE Grade 3 or 4 drug-related event (other than left ventricular cardiac dysfunction or interstitial pneumonitis) has occurred, the investigator may discuss with the GSK Medical Monitor whether a reduction of dose is appropriate.

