## 3.5 Management of Toxicity

**3.5.1 Criteria for Evaluating Cardiac and Respiratory Events**

**3.5.1.1 Asymptomatic Events**

Subjects who have a ≥ 20% decrease in left ventricular cardiac ejection fraction (LVEF) relative to baseline, and the LVEF is below the institution's lower limit of normal, should have a repeat evaluation of ejection fraction 1-2 weeks later while still receiving investigational product.

If the repeat ejection fraction evaluation confirms a ≥ 20% decrease in LVEF relative to baseline, and the ejection fraction is below the institution's lower limit of normal, then investigational product should be temporarily discontinued.

If the LVEF recovers during the next 3 weeks, after consultation and approval by the GSK Medical Monitor, the subject may be restarted on study treatment at a reduced dose. For such subjects, monitoring of LVEF will then be performed 2 weeks and 4 weeks after re-challenge, and then every 4 weeks thereafter.

If repeat ejection fraction evaluation still shows a decrease ≥ 20% in LVEF relative to baseline and the value is below the institution's lower limit of normal, then the subject should be withdrawn from investigational product. Ejection fraction should continue to be monitored every 4 weeks for at least 16 weeks or until resolution.

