**Table 6. Lapatinib Starting Dose and Dose Reduction Schedule**

| Starting dose | 1500 mg/day | *** Patients requiring a third dose reduction should be taken off study unless in the opinion of the investigator & GSK Medical Monitor, there is reason to believe that the patient is still experiencing clinical benefit |
| --- | --- | --- |
| First dose reduction | 1250 mg/day |

* if no recovery after 3 weeks of holding drug, patients should go off study unless in the opinion of the investigator & GSK Medical Monitor, there is reason to believe that the

patient is still experiencing clinical benefit.

**Table 7**. Dose Reduction Criteria and Guidelines for Management of lapatinib Associated Toxicity

|  | Grade | **Guideline for management** | **lapatinib dosage modification*** |
| --- | --- | --- | --- |
| Diarrhea | 1 | No intervention | None |
| 2 | Loperamide (4 mg at first onset,  followed by 2 mg every 2–4 hrs  until diarrhea free for 12 hrs) | None; If unacceptable to patient or medically concerning then hold until recovery  to < grade 1, up to 21 days*. Restart at same dose**. |
| > 3 (*despite optimal*  *use of loperamide)* | Hold until recovery to < grade 1, up to 21 days*. And then reduce 1 dose level. |
| Rash | 1 | No intervention | None |
| 2 | Any of the following:  minocycline+, topical  tetracycline or clindamycin,  topical silver sulfadiazine,  diphenhydramine,  oral prednisone (short course) | None; If unacceptable to patient or medically concerning then hold until recovery  to < grade 1, up to 21 days*. Restart at same dose**. |
| > 3 | Hold until recovery to < grade 1, up to 21 days*. And then reduce 1 dose level. |
| Other  Toxicity **(excluding**  **left ventricular**  **dysfunction and**  **pneumonitis,**  **see below)** | 1 | No Intervention | None |
| 2 | Treatment as appropriate | None; If unacceptable to patient or medically concerning then hold until  recovery to < grade 1, up to 21 days*. Restart at same dose **. |
| 2 prolonged or  clinically significant  and grade > 3 | Treatment as appropriate | Hold until recovery to < grade 1, up to 21 days and then reduce 1 dose level* |

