| * if no recovery after 3 weeks of holding drug, patients should go off study unless in the opinion of the investigator & GSK Medical Monitor, there is reason to believe that the patient is still experiencing clinical benefit.  ** if dose has been previously held for grade 2 toxicity and grade 2 symptoms recur, OR if the patient finds the symptoms unacceptable, hold dose until recovery to < grade 1 and then reduce dose one level  + recommended dose: 200mg po bid (loading dose), followed by 100mg po bid for 7-10 days | | | |

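### Section 3.6.1 and Tables 6 and 7 set different limits for a toxicity hold (2 weeks against 21 days), so the default action and the consultation trigger conflict on days 15 to 21

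*Protocol*

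**What the plan says.** Section 3.6.1 of the protocol sets the general rule: "Treatment may be delayed, up to 2 weeks, to allow for resolution of toxicity". The stated exception is Grade 3 or 4 left ventricular dysfunction or interstitial pneumonitis. Past 2 weeks the investigator must consult the Medical Monitor before continuing; of these patients the section says "but in general, such subjects should be withdrawn from the study". The same section requires consultation before any change in dosing.

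Table 7 gives the working instructions by toxicity and grade. Its entry for higher-grade diarrhea and rash reads "Hold until recovery to < grade 1, up to 21 days*. And then reduce 1 dose level". The grade 2 entries, where a hold is chosen, also run to 21 days and end in a restart at the same dose. The asterisk footnote, printed under both Table 6 and Table 7, sets the exit point: "if no recovery after 3 weeks of holding drug, patients should go off study unless in the opinion of the investigator & GSK Medical Monitor" see continuing clinical benefit.

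Sections 3.5.1.1 and 4.3.4 hold a separate rule for a confirmed asymptomatic fall in LVEF. It allows 3 weeks for recovery and makes restart subject to the Medical Monitor: "If the LVEF recovers during the next 3 weeks, after consultation and approval by the GSK Medical Monitor".

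**The concern.** Both limits apply to the same patients and the same toxicities. The introduction to section 3.6 makes Table 7 the schedule for lapatinib-related toxicity, and section 3.6.1 is equally directive. An investigator with a patient on day 18 of a hold finds two different defaults and two different points at which the Medical Monitor has to be called.

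Two things are at stake. The first is the management of individual patients and the ability to audit it: a restart on day 18 that follows Table 7 may be a deviation from section 3.6.1. The second is the data. The primary outcome is the effect on HER2-positive CTC counts, measured monthly in a planned 20 patients. Whether a patient stays on treatment decides whether she supplies further monthly counts.

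**Working it through.** The check is a comparison of texts. The protocol states no computed figure on this point.

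**Inputs**

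| Source | Scope | Limit | What follows beyond it |
|---|---|---|---|
| 3.6.1 | Toxicity generally, except Grade 3 or 4 left ventricular dysfunction or pneumonitis | 2 weeks = 14 days | Consult before continuing; withdrawal as the general outcome |
| Table 7 | Diarrhea, rash, other toxicity (the last excluding left ventricular dysfunction and pneumonitis) | 21 days | See footnote |
| Footnote, Tables 6 and 7 | Any hold | 3 weeks = 21 days | Off study, unless investigator and Medical Monitor see continuing benefit |
| 3.5.1.1, 4.3.4 | Confirmed asymptomatic LVEF fall | 3 weeks | Withdrawal if the fall persists; restart on recovery needs Medical Monitor approval |

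**Step 1: width of the conflict.** 21 − 14 = 7 days, that is, days 15 to 21 of a hold.

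**Step 2: is either limit a slip?** Section 3.6.1 uses 2 weeks as its trigger three times, including for delays unrelated to toxicity. Table 7 gives 21 days in six cells (two each for diarrhea, rash and other toxicity), and the footnotes repeat 3 weeks. Each limit is used consistently within its own text.

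**Step 3: is one a special case of the other?** For diarrhea, rash and other toxicity, no. Table 7 covers essentially the toxicities left to section 3.6.1 after its exceptions, and nothing states precedence.

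**Step 4: default action on days 15 to 21.** Under 3.6.1: consult before continuing, with withdrawal as the general outcome. Under Table 7: keep holding and restart on recovery, with no off-study trigger yet.

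**Step 5: consultation.** The duration-based trigger is more than 14 days in 3.6.1. In the footnotes the Medical Monitor enters only after 3 weeks without recovery, on a clinical-benefit test that 3.6.1 does not contain. Where the hold ends in a dose reduction, 3.6.1 requires consultation anyway, so the practical gap there is small. It remains for grade 2 holds restarted at the same dose: a restart on day 18 needs no call under Table 7 and needs one under 3.6.1.

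**Step 6: scale.** One patient is 1/20 = 5% of the planned cohort. Table 3 shows drug-related diarrhea in 54% and rash in 33% of patients at 1500 mg, but these are all-grade figures. The protocol gives no rate of holds longer than 14 days, so the expected number of affected patients cannot be computed.

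**The case against.** A reader might infer that after day 14 a patient is simply withdrawn under one rule and retained under the other. The text does not go that far. Section 3.6.1 states a general expectation and leaves room to continue after consultation; the footnotes also allow an exception agreed with the Medical Monitor. What conflicts is the default and the consultation trigger.

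A reader might also count the 3-week LVEF rule as a third contradiction. That is not supported. The rule is specific to one event, Table 7's other-toxicity row excludes left ventricular dysfunction, and restart already needs Medical Monitor approval, which meets the consultation requirement of 3.6.1. Both can be followed. What remains is a missing cross-reference, because the exception in 3.6.1 names only Grade 3 or 4 dysfunction.

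On consequences, the objection has force. Sections 3.3.3.2 and Table 5 keep adverse-event follow-up for 30 days after the last dose and schedule a CTC assessment at discontinuation. The toxicity is therefore recorded and a final count is planned under either rule; only later monthly counts are lost.

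Long holds may also be uncommon. Section 1.3.3.2 reports that 97% of subjects in the earlier monotherapy studies took treatment on at least 80% of days, with a median duration of 8 weeks. At 56 days, a 15-day hold is 15/56 = 27% of days and would miss that 80% mark. This is indicative only: on treatment of 15/0.20 = 75 days or longer, such a hold would still meet it.

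None of this removes the 14-day against 21-day inconsistency.

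**Conclusion.** The inconsistency stands, as one of conflicting defaults. For diarrhea, rash and other toxicity, section 3.6.1 and Tables 6 and 7 point in different directions during a 7-day window, and they place the duration-based call to the Medical Monitor at different times, which matters mainly for grade 2 holds restarted at the same dose.

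The effect on results is limited to who remains on treatment and gives later monthly CTC counts; each such patient is 5% of the planned 20. How many would be affected is unknown. The conclusion assumes that both texts are operative, which the introduction to section 3.6 and the wording of 3.6.1 support. It takes no view on which limit is clinically right. It merits correction because it governs the handling of individual patients and compliance cannot be judged while both limits stand.

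**What to change.** Reconcile section 3.6.1 with Tables 6 and 7 and their asterisk footnotes, so that one maximum hold and one point for consulting the Medical Monitor apply to all toxicity holds. State in 3.6.1 that holds for LVEF falls follow sections 3.5.1.1 and 4.3.4, as an explicit exception if that rule is meant to differ. The choice of limit belongs to the sponsor's clinicians. The cost is an amendment of protocol wording; sample size, assessments and visit schedule need not change.

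### Section 3.6.1 and Tables 6 and 7 disagree on how many dose reductions are allowed and on the default after a toxicity hold of 15 to 21 days

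*Protocol*

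**What the plan says.** Section 3.6 makes both tables operative. It states that "Starting dose and dose modifications for unacceptable toxicity are listed in Table 6" and that, for toxicity thought to be related to lapatinib, "the daily dose of lapatinib will be decreased according to the schedule displayed in the Table 7".

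**Reductions.** Section 3.6.1 states: "Only one dose reduction is permitted per subject and subjects should not be rechallenged to a higher dose level". Table 6 gives a start of 1500 mg/day and one reduced level, 1250 mg/day. The note in the same table reads "Patients requiring a third dose reduction should be taken off study unless in the opinion of the investigator" and the Medical Monitor there is reason to expect continuing clinical benefit. For higher-grade diarrhea, Table 7 says "Hold until recovery to < grade 1, up to 21 days*. And then reduce 1 dose level". The corresponding rows for rash and other toxicity say the same in substance, and the ** footnote calls for a one-level reduction in certain Grade 2 cases.

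**Holds.** Section 3.6.1 allows a toxicity delay of up to 2 weeks. It requires Medical Monitor consultation before continuing "any subject requiring a delay of more than 2 weeks for unresolved toxicity, but in general, such subjects should be withdrawn from the study". Table 7 allows holds of up to 21 days. The * footnote, printed under both tables, says "if no recovery after 3 weeks of holding drug, patients should go off study unless in the opinion of the investigator" and the Medical Monitor there is continuing benefit.

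**Oversight.** Section 3.6.1 also says "the GSK Medical Monitor must be consulted prior to implementing any change in dosing".

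**The concern.** These are dosing instructions that site staff follow when a patient has toxicity, and a later analysis plan would not settle them. Two situations are affected.

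- A patient already reduced to 1250 mg/day meets a Table 7 reduction criterion again. Section 3.6.1 bars a further reduction, Table 7 orders one, and the Table 6 note does not yet remove her.
- A patient recovers between day 15 and day 21 of a hold. Under 3.6.1 she would in general be withdrawn; under Table 7 she may restart.

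The first matter is one of safety and of consistent handling. There is also a consequence for the data: in a single-arm study of 20 patients, withdrawal or restart decides whether a patient goes on to give further monthly on-treatment CTC counts.

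**Working it through.** The protocol states no figure to reproduce here. The check sets the rules side by side.

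| Rule | Section 3.6.1 | Table 6 | Table 7 |
|---|---|---|---|
| Reductions allowed | 1 | Dose rows: 1 level (1250 mg/day). Note: off study at the third | One level down, no limit mentioned |
| Toxicity hold | Up to 2 weeks, then consult; in general withdraw | * footnote: off study after 3 weeks without recovery, with a benefit exception | Up to 21 days; same * footnote |

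**Step 1, reductions.** Removal at the third reduction tolerates 3 − 1 = 2 reductions, against 1 in section 3.6.1. The dose rows of Table 6 agree with 3.6.1, so within that table only the note is out of line. The second reduction that the note tolerates has no dose attached.

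**Step 2, how often Table 7 orders a reduction.** Three cells do so (diarrhea 1, rash 1, other toxicity 1), and the ** footnote adds recurrent Grade 2 symptoms after an earlier Grade 2 hold, or symptoms the patient finds unacceptable. None refers to the limit. Section 3.5.1.1 adds another route to 1250 mg/day, because restart after LVEF recovery is at a reduced dose and so uses up the only reduction.

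**Step 3, holds.** Six Table 7 cells carry the 21-day limit (diarrhea 2, rash 2, other toxicity 2). The difference from 3.6.1 is 21 − 14 = 7 days, that is, days 15 to 21.

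**Step 4, reach of the benefit exception.** It begins at a third reduction or after 3 weeks of holding. It covers neither a second reduction nor days 15 to 21, which is where the rules differ.

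**Step 5, precedence.** Section 3.6 invokes both tables, and nothing there or in 3.6.1 says which text prevails.

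**The case against.** The strongest reply is that the protocol can be read coherently.

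On reductions, the limit in 3.6.1 is categorical, Table 6 lists one reduced level, and Table 7 need not repeat a limit stated elsewhere. Only the Table 6 note disagrees, and it cannot be carried out because no lower dose exists. On holds, the texts can be read as steps: up to day 14 without the Medical Monitor, days 15 to 21 with the Monitor, and off study after day 21 unless there is benefit.

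Much of this stands. A reader might infer that a patient at 1250 mg/day has no route forward at all. The documents do not support that: 3.6.1 bars a further reduction and requires Monitor consultation before any dose change, and section 3.3.3.1 lets the investigator discontinue a patient for safety reasons. A reader might also infer that the hold rules are opposite commands. They are not, because the 2-week rule says only what should happen in general, and 21 days is an upper limit.

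What remains is narrower but real. The Table 6 note is wrong against 3.6.1 and against its own dose rows. The stepwise reading of the holds has to be supplied by the reader and runs against the general withdrawal default for days 15 to 21. Consultation limits the harm but does not tell the Monitor which default applies.

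**Conclusion.** The point holds as an internal inconsistency in current dosing text. On reductions, the limit of one conflicts with a note that tolerates two and with Table 7 instructions that do not refer to the limit; the outcome for a patient at 1250 mg/day is left to judgement. On holds, the default differs over a 7-day window.

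The conclusion rests on the wording alone and needs no assumption about event rates. The protocol gives no rate of holds beyond 14 days or of second reductions, so the number of patients affected cannot be estimated. A reader might go on to infer a bias in the CTC outcome; the documents show no such effect. The point deserves correction because it concerns safety and costs little, with the Medical Monitor's role as a real mitigation.

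**What to change.** 1. **Reductions.** Change the Table 6 note to: *A patient who would need a second dose reduction goes off study.* Add to Table 7: *No reduction below 1250 mg/day; a patient at 1250 mg/day who meets a criterion for a further reduction goes off study.* Patients tolerating 1250 mg/day continue. This wording ends the clinical-benefit exception for reductions, including for recurrent Grade 2 symptoms under the ** footnote. If the clinical team wants to keep the exception, the note must state that treatment continues at 1250 mg/day.

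2. **Holds.** State one rule in 3.6.1, Table 6 and Table 7, for example: *Hold for up to 14 days. Restart on days 15 to 21 only after consultation with, and agreement of, the Medical Monitor. Off study if not recovered by day 21, unless the investigator and the Medical Monitor judge that there is clinical benefit. Any restart remains subject to the limit of one reduction.* The general withdrawal clause in 3.6.1 would then no longer apply to days 15 to 21. This example takes the longer limit, so the clinical team must confirm it. If they prefer 14 days, the six Table 7 cells and the * footnotes change instead.

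The separate LVEF rule in 3.5.1.1 stays as it is. The cost is a text amendment to 3.6.1 and the two tables, with no change to visits, assessments or sample size.

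### Section 3.6.1 allows one dose reduction per subject, but the Table 6 note presupposes at least two and Table 7 sets no limit, so a second qualifying toxicity at 1250 mg/day has instructions that cannot all be followed

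*Protocol*

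**What the plan says.** Four places in the protocol govern how often lapatinib may be reduced.

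- **Section 3.6.1** sets a per-subject limit: "Only one dose reduction is permitted per subject and subjects should not be rechallenged to a higher dose level". It also requires consultation with the medical monitor before any change in dosing.
- **Table 6** gives two dose rows: "Starting dose | 1500 mg/day" and "First dose reduction | 1250 mg/day". Its note reads: "Patients requiring a third dose reduction should be taken off study unless in the opinion of the investigator & GSK Medical Monitor" see reason to think the patient is still benefiting.
- **Table 7** gives this action in its highest-grade rows for diarrhea and rash: "Hold until recovery to < grade 1, up to 21 days*. And then reduce 1 dose level". The row for other toxicity gives the same action, and there it also covers prolonged or clinically significant grade 2 events. That row excludes left ventricular dysfunction and pneumonitis. The double-asterisk footnote covers grade 2 symptoms that recur after an earlier hold, or that the patient finds unacceptable: "hold dose until recovery to < grade 1 and then reduce dose one level".
- **Section 3.6**, opening paragraph, says that for toxicity thought to be due to lapatinib the daily dose will be lowered as Table 7 sets out.

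Cardiac events are handled separately. After a confirmed asymptomatic fall in ejection fraction that then recovers, Section 3.5.1.1 says that, with the medical monitor's approval, "the subject may be restarted on study treatment at a reduced dose". Section 4.3.4 says the same.

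**The concern.** The limit in Section 3.6.1 and the off-study trigger in the Table 6 note describe different schemes. A rule that acts at the third reduction makes sense only if a first and a second may come before it. Section 3.6.1 rules out the second. Table 7 adds to the difficulty because its instruction depends neither on the current dose nor on whether a reduction has already been made, while Table 6 as shown has no level below 1250 mg/day.

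What is at stake is patient management. Depending on which text is followed, a patient with a second qualifying toxicity could be refused a further reduction, could be due one to a dose that is not listed, or could simply not yet meet an off-study rule. Two such patients could be handled differently, each in line with some part of the protocol.

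**Working it through.** The plan states no statistical figure here. The check is a count of permitted steps and a walk through one patient's course.

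**Count of reductions by source**

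- Section 3.6.1: maximum = 1.
- Table 6 rows: 2 levels listed, so 2 − 1 = 1 available step (1500 to 1250 mg/day).
- Table 6 note: trigger at the third reduction, so 3 − 1 = 2 reductions come before the off-study rule applies. The clinical-benefit exception means that even the third need not end participation.
- Table 7 and its footnote: one level per qualifying event, with no maximum stated.

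The note therefore implies 2 − 1 = 1 more reduction than Section 3.6.1 allows, and 2 − 1 = 1 more than Table 6 has a dose for.

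**First qualifying toxicity, patient at 1500 mg/day.** Section 3.6.1 allows a reduction, Table 7 calls for one, and Table 6 supplies the level. There is no conflict on the number of reductions.

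**Second qualifying toxicity, patient at 1250 mg/day, not cardiac and not pneumonitis**

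- Section 3.6.1: a further reduction is not permitted.
- Table 7, applied through Section 3.6: hold, then go down one level.
- Table 6 rows: no level shown below the current one.
- Table 6 note: the off-study trigger is not reached, because this would be the second reduction.

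The first two are directly opposed. The third leaves the second without a dose, and the fourth does not take the patient off study. No precedence rule is stated.

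**How a patient gets there.** A second step does not need a severe event, because the Table 7 footnote is triggered by recurrent or unacceptable grade 2 symptoms. Table 3 reports related diarrhea in 54% and related rash in 33% of subjects at 1500 mg once daily, and Section 1.3.3.2 says that most of the common adverse events were grade 1 or 2. The conflict is therefore foreseeable. These are rates of any related event, however, not of events that recur after a reduction, so they give no expected number among the 20 planned patients.

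**Cardiac passages.** Sections 3.5.1.1 and 4.3.4 say to stop temporarily, allow a restart at a reduced dose after recovery and approval, and withdraw the subject if the fall persists. The restart is optional, so the limit in Section 3.6.1 can apply to it without contradiction. Neither section says what happens to a subject who has already been reduced.

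**The case against.** The best defence is that Section 3.6.1 and the rows of Table 6 agree: one reduction, one reduced level. Table 7 never mentions a second reduction and can be read as operating inside that limit. The Table 6 note authorises nothing; it only says when to leave the study, and under Section 3.6.1 its condition is never met. Every dose change also goes through the medical monitor, and for grade 3 or 4 drug-related events Section 3.6.1 lets the investigator discuss with the monitor whether to reduce at all. In a single-centre pilot of 20 patients, action on one page alone is unlikely.

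Part of this stands. The figure of two reductions is inferred from the note, and the required consultation does lower the practical risk. But reading the note as dead text means choosing one passage over another, and the protocol nowhere makes that choice. Even on that reading, the action for a second qualifying toxicity is unstated, while Section 3.6 says the dose will be lowered according to Table 7. The monitor faces the same conflicting limits, and the discretion written into the Table 6 note begins only at the third reduction.

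A row of Table 6 may also have been lost when the document was read from PDF. If so, the missing-level point falls, but the clash with a limit of one becomes sharper.

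A reader might infer that the protocol also orders a reduction to an unlisted dose after a fall in ejection fraction. It does not: Table 7's row for other toxicity excludes left ventricular dysfunction, and the cardiac sections only permit a restart at a reduced dose. A reader might also infer a distorted CTC result. The documents do not show one, and two successive qualifying toxicities would seldom fall before the first on-treatment CTC assessment at week 4.

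**Conclusion.** The contradiction is real, stands in current text, and should be corrected before the protocol is used. One section caps reductions at one, a table note presupposes at least two, and a third source orders a step with no cap, while Table 6 as shown supplies one reduced level. It applies to patients at 1250 mg/day with a second qualifying toxicity other than left ventricular dysfunction or pneumonitis. The silence of Sections 3.5.1.1 and 4.3.4 on subjects already reduced is a secondary gap.

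The conclusion on the number of reductions rests only on the wording of Section 3.6.1 and the Table 6 note. The missing-level part also assumes that Table 6 is complete as shown. The number of patients affected cannot be derived from the documents: they give no rate of dose reduction and no rate of repeat toxicity after one. No view is taken on which limit or dose is right.

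**What to change.** Reconcile Section 3.6, Section 3.6.1, Table 6 with its note, and Table 7 with its footnote, so that:

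- one maximum number of reductions per subject is stated, in the same terms throughout;
- every permitted step has a dose listed in Table 6;
- one action is stated for a patient who needs more than the maximum.

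Then align Sections 3.5.1.1 and 4.3.4, so that they say what applies when the subject has already been reduced. The sponsor's clinicians and the medical monitor decide the content. The cost is protocol wording only: no extra visits, data or patients.
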